## Abstract

**Background:**

Angled manual traction (AMT) is widely used for relieving moderate-to-severe cervicobrachial pain in patients with cervical radiculopathy (CR), yet its effectiveness has yet to be established by rigorous full randomized controlled trials (RCTs). We have designed an external pilot to evaluate the feasibility of a future large-scale, definitive RCT on AMT for CR.

**Methods:**

48 CR participants with cervicobrachial pain (numeric rating scale ≥ 4) will be enrolled in a five-period pilot RCT and randomly assigned to receive either usual care alone or AMT plus usual care for 4 consecutive periods (each period defined as 7 days). The primary outcome will be feasibility, focusing on enrolment rate, retention rate, and protocol adherence. The secondary outcomes include pain in the cervicobrachial region, upper extremity numbness, muscle weakness, upper extremity and neck function, analgesic consumption (non-steroidal anti-inflammatory drugs and opiates), work ability, quality of life, emotional well-being prior to administering treatment at each period’s initial visit, as well as safety and intervention costs during the trial. We employ linear mixed-effect models on the efficacy-related outcome measures to assess the changes within and between groups over time, and determine the statistical trends of effectiveness.

**Results:**

We expect the trial to be completed by June 2026, with successful pilot targets defined as achieving ≥ 25% enrolment, ≥80% adherence, ≥80% retention, and superior health outcomes in the AMT add-on arm compared with usual care.

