## Objectives

2

The aim of this external pilot study is to ascertain the feasibility of a definitive full-scale RCT that determines whether AMT plus usual care is superior to usual care alone in clinical efficacy and cost-effectiveness regarding cervicobrachialgia reduction. In this study, we will (1) evaluate the recruitment and retention of participants, treatment adherence, and completion of proposed outcome measures to inform the feasibility and acceptability of study design; (2) and estimate the variability of efficacy-related outcomes to preliminarily inform sample size calculation for a future fully powered RCT.

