#### Data analysis

3.7.2

Data will be statistically analyzed using PASW Statistics 18.0, STATA 14.0 and R 4.3.0. Continuous variables will be summarized as means with standard deviations or medians with interquartile ranges, whereas categorical variables will be presented as counts and percentages. The primary outcome will be outlined using descriptive statistics. Building on reported positive associations between colder temperatures, male sex, and more consultations for musculoskeletal pain (76), we will conduct subgroup analyses to explore how season and sex influence enrolment, retention, and adherence, thereby informing weather-adaptive management strategies for the future full RCT. Secondary outcome measures will be analyzed based on the intention-to-treat population approach. Any post-randomization participants who received at least one intervention session will be included in the full analysis set. Among these, those who completed at least 80% of the planned treatments without any significant protocol violations will be categorized into the per-protocol analysis set. Any post-randomization participants receiving at least one intervention session will be classified into the safety analysis set. Any missing data will primarily be handled using multiple imputation, with last observation carried forward applied for sensitivity analysis.

We will analyze both within- and between-group changes for each efficacy-related secondary outcome variable using a linear mixed-effects model to derive estimates of intervention effects.

Group allocation, time-point and the interaction between group allocation and time-point will act as fixed-effects, individuals as random effects, and baseline measurements as covariates. Given that this exploratory trial is not formally powered to assess effects, a recommended confidence interval of 75% will be employed to infer the size and direction of the calculated effect estimates (77). The 75% confidence interval will be compared with the MCIDs to preliminarily assess whether the difference between treatment groups holds potential for clinical significance (77). The remaining secondary outcome measures involving AER, ARR, and intervention costs, as well as baseline variables, will be presented descriptively by the groups.

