## Results

4

Recruitment for the pAMTLER began on 1 August 2024. Thirty-three patients have been recruited as of 31 July, 2025. The trial was originally scheduled to end in August 2025. However, due to slow recruitment, the trial may have to be extended to late June 2026. We expect participant recruitment to conclude in late December 2025, data collection to be finished in late February 2026, and results to be available and published in late June 2026.

Successful pilot targets are defined as a ≥ 25% enrolment rate, a ≥ 80% adherence rate as well as a ≥ 80% retention rate (78, 79). The trial may be infeasible if enrolment is <15%, adherence is <70%, or retention is <70%. Therefore, strong measures should be taken to improve feasibility. Additionally, we hypothesize that the AMT add-on arm will result in better health outcomes than the usual care control arm. The study results will be disseminated through open-access peer-reviewed journals, scientific conferences, and public channels.

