## Discussion

5

A full RCT with appropriate power is necessary to establish the clear effects of AMT on pain relief and functional improvement in patients with CR. However, such studies conducted over the past decade have been insufficient. Therefore, establishing whether a more extensive future RCT would be viable is of paramount importance (78). The pAMTLER study is a randomized pilot developed to address this issue. It will focus on assessing the ability to enroll CR individuals with moderate-to-severe cervicobrachialgia, to retain participants for the intervention duration, and to encourage participants to adhere to the protocol during the trial, thereby establishing the feasibility of a proposed full-scale RCT. Meanwhile, the pAMTLER study can provide preliminary data on the efficacy and safety of AMT for CR, thereby complementing the key estimates regarding outcome variability necessary for sample size calculations in the confirmatory trial.

Several advantages make the pAMTLER study instructive for a future definitive RCT on AMT for CR. To begin, the pAMTLER study meets the methodological requirements for feasibility and pilot projects. It was carefully designed, not only with adequate randomization, allocation concealment, and blinding of outcome assessors and statisticians, but also specifying clear feasibility objectives, analytic plans, and criteria for the success of feasibility (80). Additionally, with small feasibility study samples, confidence intervals for clinically important differences in outcomes of interest are narrowed to a 75% confidence level. Such analytical strategies are justified, contributing to realistic and unbiased effect estimates to inform subsequent power calculation for the future full definitive RCT (77, 79). Third, unlike most previous RCTs which directly compare different multimodal conservative strategies for CR patients (20, 81), the pAMTLER study is characterized by a randomized add-on trial. An add-on study design could be more rational in circumstances where analgesics are commonly preferred as the first-line therapy (82), while also allowing for further understanding of AMT’s superiority in real-world clinical practice of CR.

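### The abstract counts superior health outcomes as a fourth pilot success target, against three feasibility targets in section 4; section 5 wrongly credits 75% intervals with unbiased effect estimates for the power calculation

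*Protocol article*

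**What the plan says.** **Success rule.** The abstract (Results) lists at least 25% enrolment, 80% adherence and 80% retention as the pilot's success targets, and then adds "and superior health outcomes in the AMT add-on arm compared with usual care". Section 4 (Results) states the rule again: "Successful pilot targets are defined as a ≥ 25% enrolment rate, a ≥ 80% adherence rate as well as a ≥ 80% retention rate". It gives infeasibility limits for those three only (enrolment below 15%, adherence below 70%, retention below 70%). Better outcomes come afterwards, with a different status: "Additionally, we hypothesize that the AMT add-on arm will result in better health outcomes than the usual care control arm".

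**Design.** The abstract's Methods and section 3.6.1 make feasibility the primary outcome, and section 3.7.1 sizes the trial on feasibility rates. Section 3.7.2 says of the efficacy analysis: "Given that this exploratory trial is not formally powered to assess effects, a recommended confidence interval of 75% will be employed".

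**Later use of the data.** Section 2 sets the aim to "estimate the variability of efficacy-related outcomes to preliminarily inform sample size calculation", and the abstract's Conclusion likewise names feasibility and outcome variability. Section 5 (Discussion) first says the same. It then says that reporting at the 75% level is justified, "contributing to realistic and unbiased effect estimates to inform subsequent power calculation for the future full definitive RCT".

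**The concern.** The rule that decides whether the pilot succeeded should read the same wherever it is stated, and should be fixed before results are known. Here it does not. The extra target is also one that the trial was not designed to judge: no outcome is named among the many efficacy measures, there is no time point and no margin, and the plan itself disclaims power for effects. Whoever reports the pilot could cite either version once the data are in.

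The section 5 sentence matters because it describes what the next trial will be built on. It credits the choice of confidence level with a property that a confidence level cannot confer, and it names the effect estimate as an input where the objectives name only variability.

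**Working it through.** **1. The two rules side by side**

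| Pilot result | Abstract, Results | Section 4 |
|---|---|---|
| Three thresholds met, AMT better | success | success |
| Three thresholds met, AMT not better | not a success | success |
| Any threshold missed | not a success | not a success |

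The rules disagree in the second row. The abstract does not merely condense section 4; it adds a condition.

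**2. How the extra target would behave**

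The plan gives no effect-based sample size or power figure to reproduce. Its 48 comes from the precision of feasibility rates, and this point does not depend on that calculation. No SD is given either, so effects are in SD units and their sizes are assumptions.

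Inputs: 24 in the experimental arm (section 3.1) with 1:1 allocation (section 3.4), so 24 per arm; 75% interval (section 3.7.2). Assumptions: no drop-out, an unadjusted comparison of two means, and the target read as a 75% interval wholly in favour of AMT. The plan does not state that reading.

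- Standard error of the difference: √(2/24) = 0.289 SD.
- Half-width at 75%: 1.150 × 0.289 = 0.33 SD.
- Half-width at 95%: 1.960 × 0.289 = 0.57 SD.
- Chance that the 75% interval lies wholly in favour of AMT, with d the true effect in SD units: Φ(d/0.289 − 1.150).

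| Assumed true effect d | d/0.289 | Chance the target is met on one outcome |
|---|---|---|
| 0 | 0 | Φ(−1.150) = 12.5% |
| 0.3 | 1.039 | Φ(−0.111) = 46% |
| 0.5 | 1.732 | Φ(0.582) = 72% |
| 0.8 | 2.771 | Φ(1.621) = 95% |

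On this reading, a fully feasible pilot of a treatment with a true 0.3 SD effect would miss the abstract's fourth target in about 54% of trials (100 − 46). If the target were judged on the sign of the point estimate, a treatment with no effect would meet it half the time on any one outcome.

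**3. Confidence level and bias**

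The interval is estimate ± z × SE. Going from 95% to 75% changes z from 1.960 to 1.150. The estimate and the SE stay where they were, so the half-width falls from 0.57 to 0.33 SD with no gain in information and no change in bias. Whether the estimate is unbiased depends on randomisation, measurement and missing data. The limitations paragraph of section 5 itself says that unblinded self-report may introduce measurement bias, which sits badly with calling the estimates unbiased.

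**The case against.** **The body text should govern.** The fourth target appears once, in an abstract sentence that mixes expected results with targets. Section 4 is explicit about three criteria, and nothing in the body makes progression depend on efficacy. This stands as a reason to think that three criteria are meant. It does not remove the contradiction, because both places claim to define success.

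**The arithmetic assumes a rule.** Section 3.7.2 compares the 75% interval with MCIDs, not with zero, and its model uses baseline and repeated measures, which would shrink the standard error. This stands too, so the percentages above are for scale only. It also shows that the target cannot be judged as written.

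**Stronger readings that the documents do not support:**

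- *Near-certain false success.* A reader might compound the 12.5% over all the efficacy measures. That assumes that any one favourable outcome suffices and that outcomes are independent. No section states such a rule, and pain, neck disability and arm disability scores are plainly related.
- *An underpowered definitive trial.* A reader might infer that a favourable pilot effect will first be required and then used to set the sample size. That needs the abstract clause to act as a gate and the pilot effect to serve as the target difference. Section 5 says only that estimates will inform the calculation, and it names variability a paragraph earlier.
- *A missing recruitment-pace criterion.* Weekly enrolment is listed without a threshold although "due to slow recruitment, the trial may have to be extended to late June 2026". Drop-out and completion rates have no separate threshold either. Leaving a descriptive measure without a cut-off is not an error, and one set now would be post hoc.

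**Conclusion.** The point holds in two parts, both wrong as written.

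1. The success rule contradicts itself. The abstract has four targets and section 4 has three. The fourth is undefined and conflicts with a design that section 3.7.2 calls not powered for effects. The two rules give opposite answers for a feasible pilot without an AMT advantage. The 46% and 12.5% figures rest on 24 complete participants per arm, an unadjusted comparison of one outcome and, for the 46%, an assumed effect of 0.3 SD. The contradiction itself needs none of these assumptions.
2. The section 5 sentence is statistically wrong about the 75% level and goes beyond section 2 and the abstract's conclusion on what will inform the sample size. It is one sentence against three consistent statements, so it is a drafting error to correct and not evidence of a settled plan to power on the pilot effect.

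**What to change.** - **Abstract, Results:** delete superior health outcomes from the success targets, so that the abstract and section 4 give the same three feasibility criteria. Better outcomes may stay as an exploratory hypothesis, worded as in section 4.
- **Section 5:** replace the sentence on unbiased effect estimates. Say that the pilot informs the power calculation through outcome variability, that the 75% interval only describes uncertainty about the effect, and that the pilot effect estimate will not be used as the target difference.

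The cost is two edits to wording. Sample size, conduct, data collection and the planned models are unchanged. The choice of target difference can be left to the definitive trial's protocol.

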**Conclusion:**

This external pilot trial will provide robust data on feasibility and outcome variability for power calculations in the proposed future confirmatory RCT on AMT for CR. This pilot RCT will be invaluable to the design and management of the subsequent full-scale RCT.

**Trial registration:**

Chinese Clinical Trial Registry (ChiCTR): https://www.chictr.org.cn/showproj.html?proj=236348 ChiCTR2400087289.

## Introduction

1

Cervical radiculopathy (CR) is a term used to describe a consequence triggered by mechanical compression of nerve roots within the neural foramen due to age-related degenerative changes in the cervical spine, i.e., herniated disk material, hypertrophied facet joints, and/or uncovertebral joints (1–5). It is a prevalent, debilitating cervical spine condition characterized by pain in the cervicobrachial region and abnormal neurologic signs along the path of innervation of the affected nerve root, including paraesthesia, numbness, muscle weakness and diminished deep tendon reflexes. The annual incidence has been reported to be between 0.83 and 1.79 per 1,000 person-years, with an estimated prevalence from 1.21 to 5.8 per 1,000 (6). CR is frequently described as a self-limiting disorder with a favorable prognosis (7, 8). However, pain during the first weeks to months is often excruciating (9), and most patients report experienced continuous, fluctuating pain for up to 24–36 months before achieving complete recovery (10, 11). Such pain contributes to impaired physical function, poor mental well-being, limited regular activities, and isolated social life (12–14). It has been reported that approximately 352.0 cases per 100,000 individuals worldwide have suffered from disability resulting from CR over the past three decades (15). Patients with CR are vulnerable to experiencing varying degrees of work ability impairment due to both physiological disturbances and psychological distress (13, 14, 16). Hence, they may be at a higher risk of exclusion from the labor market due to frequent sick leave, work absenteeism, and even failure to execute work duties (13, 14). Patients with CR are also believed to experience poorer economic outcomes as a result of work productivity loss, with an estimated average willingness-to-pay far exceeding $38.0 per month for a 1-point reduction in pain (17).

Relieving pain, improving neurologic function, and preventing recurrence are the primary treatment objectives to facilitate CR patients’ return to their usual activities and work (1, 3, 18). Conservative management is universally considered the first course for CR due to its favorable natural history, where non-steroidal anti-inflammatory drugs (NSAIDs) are typically the primary options, with possible escalation to opioids when pain remains uncontrolled (1, 8, 18, 19). Multimodal care combining oral analgesics with physiotherapy, which includes but is not limited to collar immobilization, traction, and manual therapy, is generally recommended as the initial prescription for CR (8, 18–20). However, the existing conservative strategies are of limited value in accelerating improvements in pain and function (20, 21). The current body of knowledge highlights a critical need for additional scalable, safe pain relief strategies for patients with CR.

Angled manual traction (AMT) is an integrative Chinese-Western protocol originating from clinical observations that forced cervical anteflexion alleviates pain in middle-aged and elderly patients with CR (22). This combined modality sequentially combines two *tuina* techniques—pressing-kneading manipulation and traction manipulation—with mechanical traction. Both are performed with the cervical spine held in anterior flexion at variable angles, which are determined by the pathoanatomic level of nerve-root compression. Over nearly two decades of CR management, AMT has shown excellent alleviation of moderate-to-severe cervicobrachialgia, with benefits presenting immediately post-treatment and extending to functional deficits (23). It has also shown considerable safety (24). Unlike the Kaltenborn method (25, 26), which is based on the concave-convex rule to restore physiological motion in hypomobile joints through graded traction and gliding, AMT appears more consistent with the pathogenesis of CR in middle-aged and elderly individuals. In these patients, neural foramen stenosis is typically caused by degenerative loss of disk height and the resulting compensatory hypertrophy of intervertebral joints to stabilize the cervical spine (27). Our ongoing biomechanics experiments on cervical cadaveric species (28) preliminarily show that the heights of intervertebral foramina at different cervical levels (C4-C5, C5-C6, and C6-C7) tend to increase with greater flexion angles (Appendix S1). During the experiments, the cervical spine specimens were subjected to a 60 N axial tensile force at various angles of anterior cervical flexion. Magnetic resonance imaging in middle-aged and elderly patients with CR (24, 29) also indicated that both the sagittal diameter and the cross-sectional area of the cervical spinal canal following AMT—characterized by applying traction to the cervical spine with the neck positioned in 20°–45° flexion—were greater than those measured when traction was performed in the neutral (0° extension) or retraction (15° extension) positions. Additionally, the upward pulling-stretching force applied along the longitudinal axis of the cervical spine during traction manipulation of AMT might elicit a more pronounced and immediate reduction in intradiscal pressure than mechanical traction alone, thereby achieving rapid pain relief (30). AMT has consequently been regarded as a viable proactive intervention for reducing surgical risks in CR patients. Anecdotally, patients with CR receiving AMT have also been observed to have faster work resumption, indicating that this complex intervention program may lower health care costs, improve economic outcomes, and thus be cost-effective.

Given the insufficiency of current conservative therapies, AMT, with its wide-ranging physical and psychological benefits, is emerging as another promising therapy for patients with CR. Nevertheless, these conclusions are largely derived from anecdotal experiences or observations of poor quality, such as those which lack systematic design and experimental comparators, as well as those with small and poorly represented samples, non-standard measures, insufficient follow-up periods, and/or incomplete reporting. Thus, the definitive role of AMT in CR remains to be established through well-designed randomized controlled trials (RCTs) with substantial sample sizes. However, the available information cannot provide robust data to inform the design and delivery of an RCT with solid methodologies. Given these considerations, we propose a small-scale pilot RCT. We hope the findings of this preliminary trial will provide valuable insight into the feasibility, design, and even management of a future full-scale RCT with adequate power.

## Objectives

2

The aim of this external pilot study is to ascertain the feasibility of a definitive full-scale RCT that determines whether AMT plus usual care is superior to usual care alone in clinical efficacy and cost-effectiveness regarding cervicobrachialgia reduction. In this study, we will (1) evaluate the recruitment and retention of participants, treatment adherence, and completion of proposed outcome measures to inform the feasibility and acceptability of study design; (2) and estimate the variability of efficacy-related outcomes to preliminarily inform sample size calculation for a future fully powered RCT.

## Materials and methods

3

